## Results

Ethics approval for this study was obtained in January 2025, and the trial was registered on ClinicalTrials.gov in February 2026. Participant recruitment is scheduled to begin in July 2026, with completion anticipated in June 2027. As of manuscript submission, participant recruitment has not yet commenced. Data analysis will commence after completion of the 3-month follow-up assessments, and the study findings are expected to be published in late 2027. The results of this pilot trial will provide evidence regarding the feasibility, safety, and preliminary efficacy of MNS in patients with cognitive dysfunction following acute TBI and will inform the design of a future definitive RCT.

## Discussion

### Principal Findings

This pilot RCT is expected to provide the first prospective evidence regarding the feasibility, safety, and preliminary efficacy of right MNS for cognitive dysfunction following acute TBI. We hypothesize that MNS will be feasible to implement during the early postinjury period, demonstrate an acceptable safety profile, and show promising signals of benefit in cognitive recovery, daily functioning, and quality of life. In addition to evaluating clinical outcomes, this study will explore changes in serum cognitive biomarkers and MEG, which may provide preliminary insights into the neurophysiological mechanisms underlying MNS. The anticipated findings will inform the design, outcome selection, and sample size estimation of a future definitive RCT.

Multiple noninvasive interventions of neuromodulation have been suggested to improve the cognitive function of TBI survivors in the chronic stage [9-12]. A key strength of this protocol is that it will be the first RCT to assess the feasibility, safety, and preliminary efficacy of MNS for improving cognitive dysfunction, daily functioning, and quality of life after acute TBI. In addition, serum cognitive biomarkers and MEG will be measured to help explain the neural mechanisms by which MNS improves cognitive function after TBI. We believe the findings from this pilot study will contribute to deciding whether to proceed with the forthcoming large-scale trial and, if needed, redesigning the protocol such as eligibility criteria, the dose of interventions, assessment schedule, and sample size. As a pilot study, the primary objective is to inform the design of a definitive trial rather than to draw firm conclusions regarding efficacy.

Compared with TMS and tDCS, MNS is more convenient and economical, has fewer side effects, and has been used to promote recovery from acute coma [12,13]. However, the effects of MNS in cognitive dysfunction after acute TBI have yet to be tested. In this study, we will limit inclusion to participants who have a moderate TBI event 7 days before recruitment and are clinically diagnosed as being in early cognitive dysfunction. Because no study to date has examined the effects of MNS on cognitive dysfunction after acute TBI, our study design and stimulation parameters are based on findings from patients with acute TBI-related coma. In our previous study involving participants with a traumatic coma 7 to 14 days after brain injury, right MNS stimulation 8 hours per day for 2 weeks showed clinically meaningful effects on emergence from coma, level of consciousness, and functional outcomes [13]. Therefore, the intervention is initiated in the early postinjury period and lasts for 2 weeks.

### Limitations

The present study has some potential limitations. First, the study aims to enroll patients with moderate TBI. Therefore, the findings should be interpreted with caution, particularly when generalizing to patients with mild or severe TBI. Second, because the sham intervention does not produce sensory and motor responses comparable to active MNS, participant blinding cannot be fully guaranteed, which may introduce expectancy effects and performance bias. This limitation should be considered when interpreting the study findings. Furthermore, results will only reflect short-term effects as the treatment duration will be only 2 weeks, and differences in patient lifestyles, treatment, and rehabilitation during the follow-up period may affect results. Therefore, we will collect relevant data during the follow-up period and adjust statistical analyses if needed.

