### Interventions

Participants will receive right MNS (active or sham) for 2 consecutive weeks in addition to standard care. During the intervention period, medications that may affect cognitive function will not be permitted. The median nerve stimulator (XCH-B1; Jiangxi Nuocheng Electric Co Ltd) delivers asymmetric biphasic pulses. In the active MNS group, stimulation will be delivered at a fixed frequency of 40 Hz with a pulse width of 300 µs using a 20-second ON or 40-second OFF duty cycle. During the first treatment session, the treating investigator will set the stimulation intensity between 15 and 20 mA according to individual tolerance. The intensity may subsequently be adjusted within this range if necessary to maintain a visible thumb flexion while remaining comfortable and well tolerated by the participant. Participants in the sham group will use an identical device with the same electrode placement, treatment duration, and operating procedures as those in the active MNS group. However, the device will be programmed to deliver 0 mA, thereby providing no electrical stimulation. This sham procedure was selected to control for the nonspecific effects associated with device application while avoiding unintended activation of the median nerve. Participants will be instructed not to modify the stimulation parameters independently. Any adjustment to the stimulation intensity will be performed only by the study investigator when clinically indicated.

Two self-adhesive surface electrodes will be placed over the right median nerve on the volar aspect of the forearm. The distal electrode (anode, +) will be positioned approximately 2 fingerbreadths proximal to the wrist crease, and the proximal electrode (cathode, −) will be positioned approximately 2 fingerbreadths proximal to the distal electrode along the course of the median nerve. Before the first treatment session, study personnel will verify correct electrode placement and provide standardized instructions regarding the intervention procedure. The stimulation site will be inspected before each treatment session for erythema, irritation, blistering, or other signs of skin injury.

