### Study Plan

Patients with TBI are routinely screened on the seventh day after injury. If cognitive dysfunction is detected, the patient may be eligible to participate according to the inclusion and exclusion criteria. Eligible patients will be informed about the study and provided with an information leaflet. If the patient is willing to participate, an appointment will be scheduled.

#### Visit 1

At the initial visit, which will be the seventh day after injury, written informed consent will be confirmed, and the participant will then be allocated to a group. Demographic data and results of neurological examinations will be collected. Neurological function, cognitive function (via scales, MEG, and serum biomarkers), mental behavior, activity of daily living, and quality of life will be assessed. Afterward, the participant will receive a median nerve stimulator and will receive brief training and instructions. Then the stimulation phase for 2 weeks starts. The treatment will be performed in the hospital under the supervision of trained study staff. The participant is advised to contact the principal investigator during interventions if any side effects occur.

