#### Visit 3 (3 Months After Injury)

The last visit will be 3 months after injury. In this follow-up phase, the persistence of the MNS effect will be evaluated to determine whether it is sustained or diminishes over time. At the last visit, neurological function, cognitive function, mental behavior, activity of daily living, and quality of life will be assessed for the third time, and the safety data will also be evaluated again.

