### Blinding

Investigators in charge of the recruitment and follow-up evaluation, outcome assessors, and data analysts will be blinded to group allocation. Participants and independent researchers who apply the MNS will not be blinded. Researchers who monitor patients’ safety and perform risk management can access group allocation if necessary. Before the outcome assessment begins at every follow-up evaluation, the participants will be reminded not to reveal any information about their group allocation to decrease the risk of unblinding. If the investigator can detect details of group allocation during follow-up, another blinded researcher will evaluate the outcome. To minimize performance bias, participants in both groups will receive identical standard care, follow the same treatment schedule and assessment procedures, and be managed according to the same clinical protocol throughout the study.

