### Data Analysis

The feasibility outcomes will be reported using descriptive statistics. Recruitment, enrollment, adherence, and retention rates will be presented with 95% CIs. AEs and their frequency will also be summarized descriptively. Participant-reported symptom and acceptability questionnaire scores will be summarized using frequencies, percentages, medians, and IQRs, as appropriate. Baseline demographic and clinical characteristics will be summarized descriptively by the treatment group. No formal statistical significance testing will be performed for baseline characteristics. Exploratory cognitive outcomes will be analyzed according to the intention-to-treat principle where applicable. Missing outcome data will be handled using multiple imputation if appropriate. As this is a pilot feasibility trial with a small sample size, efficacy analyses are exploratory and are not powered to demonstrate definitive treatment effects. Group differences will be estimated using appropriate statistical methods according to the data distribution, with emphasis placed on effect sizes and 95% CIs rather than statistical significance. No formal adjustment for multiple comparisons will be performed. The estimated effect size for the MMSE will be used to inform the sample size calculation for the future definitive RCT.

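### Adjusting group comparisons for treatment, rehabilitation and lifestyle during follow-up can bias the randomised effect, because these variables arise after allocation

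*Protocol article*

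**What the plan says.** The Limitations section warns that "differences in patient lifestyles, treatment, and rehabilitation during the follow-up period may affect results". As the direct consequence it then states that "we will collect relevant data during the follow-up period and adjust statistical analyses if needed". It names no trigger, covariate list, outcome or method, and does not say whether the adjusted analysis would be the main or a supplementary one.

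Other sections that bear on the point:

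- **Timing of allocation.** At Visit 1, on day 7 after injury, "written informed consent will be confirmed, and the participant will then be allocated to a group". Stimulation then runs for 2 weeks. Outcomes are assessed at 1 month and again at 3 months: "The last visit will be 3 months after injury".
- **Blinding.** "Participants and independent researchers who apply the MNS will not be blinded". The same section says that "participants in both groups will receive identical standard care, follow the same treatment schedule and assessment procedures".
- **Concomitant medication (Interventions).** "During the intervention period, medications that may affect cognitive function will not be permitted". This restriction covers only the 2-week intervention period.
- **Data Analysis.** "Exploratory cognitive outcomes will be analyzed according to the intention-to-treat principle where applicable". The section names no covariates and does not mention the adjustment. It says that the MMSE effect size will inform the sample size of the definitive trial.

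**The concern.** Randomisation balances, in expectation, everything that exists before allocation. It gives no such protection for what happens afterwards. Rehabilitation, other treatment and lifestyle during follow-up can be consequences of the arm in two ways:

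- Participants know what they received and may seek or decline other care accordingly.
- If stimulation helps cognition and daily functioning, as the Discussion hypothesises, better function can change the rehabilitation and daily life that follow.

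These variables also share unmeasured causes with cognition, such as injury severity and recovery potential. Holding them fixed can remove the part of the effect that runs through them. It can also open a non-causal path between arm and outcome through the shared cause. Either way the adjusted contrast no longer estimates the total effect of being randomised to stimulation.

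The conditional wording adds a second problem. With 15 participants per arm, the choice of covariates can move the estimate noticeably, and nothing stated prevents that choice from following the data.

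At stake is how the exploratory efficacy estimates are interpreted and, through the MMSE estimate, the planning of the definitive trial.

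**Working it through.** The plan states no figure on this point, so there is nothing to reproduce. The check has three parts: timing, the form of the bias, and an illustration. **All coefficients below are assumptions; the documents supply none.**

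**1. Timing.** Allocation is on day 7 and stimulation ends at about day 7 + 14 = 21. Taking a month as 30 days, the 1-month visit falls about 30 - 21 = 9 days after stimulation ends, and the 3-month visit about 90 - 21 = 69 days after. All follow-up variables are therefore post-randomisation, and the 3-month outcomes have far more time to be affected by them.

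**2. Form of the bias.** Let T be arm, R a follow-up variable such as rehabilitation, and U an unmeasured cause such as severity, with

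- R = aT + cU + error
- Y = τT + bR + gU + error

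Both R and Y are scaled to SD 1 within arm. The total randomised effect is τ + ab. Regressing Y on T and R gives τ - agc for the arm. Hence

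bias = (τ - agc) - (τ + ab) = -a(b + gc).

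The bias is zero if a = 0, that is, if the arm does not affect R.

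**3. Numbers (SD units).** The simulated column is the mean over 20,000 trials of 15 per arm, rounded.

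| Scenario | a | b | c | g | True total | -a(b + gc) | Simulated adjusted estimate |
|---|---|---|---|---|---|---|---|
| R not affected by arm | 0 | 0.3 | 0.4 | 0.4 | 0.50 | 0 | 0.50 |
| R on the causal path only | 0.5 | 0.3 | 0 | 0 | 0.50 | -0.15 | 0.35 |
| Same, with shared cause | 0.5 | 0.3 | 0.4 | 0.4 | 0.50 | -0.23 | 0.27 |
| Same, sicker patients get more rehabilitation | 0.5 | 0.3 | 0.4 | -0.4 | 0.50 | -0.07 | 0.43 |
| No true effect, shared cause | 0.5 | 0 | 0.4 | 0.4 | 0 | -0.08 | -0.08 |
| No true effect, opposite sign of g | 0.5 | 0 | 0.4 | -0.4 | 0 | +0.08 | +0.08 |

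Without R in the model, the simulated estimate was 0.50 where the truth is 0.50 and 0.00 where it is 0, in every scenario.

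**A stronger assumed case, in MMSE points.** Suppose there is no true effect, MMSE = 3U + error (SD 2), and rehabilitation = 0.8T + 0.6U + error (SD 1). The within-arm slope of MMSE on rehabilitation is (0.6 × 3)/(0.36 + 1) = 1.8/1.36 = 1.32. The spurious arm effect is -0.8 × 1.8/1.36 = -1.06 points. The MMSE SD is √(9 + 4) = 3.6, so this is -0.29 SD. Because stimulation is assumed to have no effect here, the arm difference in rehabilitation could come only from behaviour such as care-seeking by unblinded participants, not from better recovery.

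**4. What it would do to planning, if it reached the planning estimate.** With two-sided alpha 0.05 and 80% power (both assumed), n per arm = 2(1.960 + 0.842)²/d². For d = 0.50 this is 2 × 7.85/0.25 = 62.8, rounded up to 63, or 126 in total. For d = 0.35 it is 2 × 7.85/0.1225 = 128.2, rounded up to 129, or 258 in total.

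**The case against.** - **The sentence is tentative and sits in Limitations.** It is conditional and names no model, and Data Analysis does not repeat it. A reader might infer that the main MMSE comparison will be adjusted this way and is therefore biased. The text does not support that: adjustment is only a possibility, and bias needs the arm to affect the variable. Still, it is a stated analysis intention tied to follow-up variables, and nothing in the article limits it to baseline values or labels it supplementary.
- **Safeguards in the design.** Identical standard care, supervised in-hospital treatment and the medication restriction all limit differences between arms. They act mainly during the intervention. The Limitations section itself expects differences afterwards.
- **The 1-month MMSE is little exposed.** Only about 9 days separate the end of stimulation from that visit. If follow-up means the phase leading to the 3-month visit, as the Visit 3 text suggests, these variables arise after the 1-month MMSE and could not sensibly be its covariates. This largely stands, although follow-up is used more broadly under Blinding.
- **Intention to treat.** A reader might infer a contradiction with the intention-to-treat statement. There is none: a covariate does not change who is analysed or in which arm. What changes is the effect being estimated.
- **Covariate lists and triggers belong in the SAP.** True, and their absence is not the complaint. The complaint is the kind of variable named.
- **Low stakes.** Efficacy is exploratory and does not decide progression. With 15 per arm the standard error of an unadjusted difference is about √(2/15) = 0.37 SD, larger than every bias shown. This limits the weight of the point. It does not make the adjustment sound, since a systematic error is not excused by a wide interval.

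**Conclusion.** The point holds as a correctable flaw in a stated analysis intention. Adjusting group comparisons for treatment, rehabilitation or lifestyle during follow-up can bias them for the total randomised effect, and doing so at discretion adds data-driven model selection.

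Size and direction are unknown. In the assumed scenarios the bias lies between 0 and about -0.3 SD, and with no true effect it can also be positive (+0.08 SD in one case). The figure of -1.06 MMSE points should not be read as an expected error, because it comes from one chosen set of coefficients. The conclusion rests on the arm being able to influence these variables. The unblinded design and the trial's own hypothesis make that plausible, but the documents do not establish it.

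The 3-month outcomes carry most of the risk. The 1-month MMSE change carries less, so the rise from 126 to 258 shows only what could follow if an adjusted estimate were used for planning. Because efficacy is exploratory and does not govern progression, this is a change that should be made rather than a fault that undermines the pilot.

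**What to change.** Replace the last sentence of the Limitations section with wording to this effect, and carry it into Data Analysis:

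> Treatment, rehabilitation and lifestyle during follow-up will be recorded and summarised by arm. The main group comparisons will use only pre-specified baseline covariates (for example baseline MMSE) and no variable measured after randomisation. Any analysis that uses follow-up variables will be pre-specified, labelled as supplementary, and not used for the effect size that plans the definitive trial.

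This does not ban follow-up variables from every analysis. A supplementary analysis with a clearly stated target remains possible. Baseline MMSE is an example, and the choice of baseline covariates stays with the trial team.

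The cost is a short change of text. Data collection, visits and sample size are unchanged. The Results section says that recruitment had not begun at submission, so on that timetable the change can be made before any outcome data exist.

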### Conclusions

If the predefined feasibility criteria are met, the findings from this pilot study will support the development of a fully powered RCT to further evaluate the clinical effectiveness of MNS in patients with cognitive dysfunction following acute TBI. The study results will be disseminated through publication in peer-reviewed journals and presentations at national and international scientific conferences. Trial results will also be reported in the clinical trial registry in accordance with applicable reporting requirements.
